## Methods/Design

### Study design

We will incorporate exploratory and explanatory components in a mixed methods embedded design [24]. Thus, we will embed semi-structured qualitative interviews within a pilot randomised controlled trial of Morita Therapy plus treatment as usual versus treatment as usual alone for people with depression, with or without anxiety disorders. We will give quantitative and qualitative components equal priority and mix them interactively at the design level within a program-objective framework [24]. For these two components, we will collect data concurrently and analyse data simultaneously. We will use quantitative data to assess the feasibility of trial recruitment, retention and treatment adherence, and to inform any future sample size calculations. We will collect qualitative data on participants’ and therapists’ views of Morita Therapy. By merging qualitative and quantitative data, we aim to explain variability in participants’ treatment adherence and develop a richer understanding of the feasibility, acceptability and appropriateness of Morita Therapy (Table 1).

### Philosophical assumptions

Our decision to use a mixed methods design is driven by the primary importance we give to addressing the uncertainties associated with running a fully-powered RCT. Thus, we are guided by a pragmatic philosophy: we prioritise our research objectives and the methods which will lead to the best evidence with regards to those objectives [25]. Consistent with a pragmatic worldview, we will also approach the objectives from a pluralistic perspective, combine deductive and inductive modes of reasoning, and allow for a singular view and multiple views of reality in how we come to understand and interpret our findings [25].

### Pilot Randomised Controlled Trial

#### Sample size

A conventional power calculation is inappropriate for the purpose of a pilot trial [20]. Instead, we have calculated the sample size in order to provide useful information about the aspects of the study being assessed for feasibility [20]. Thus, we have constructed confidence intervals based on certain criteria for success [20], specifically: recruiting at a rate of 12 % of those invited and experiencing an attrition rate no higher than 20 % of those randomised. We expect to invite a total of 570 participants to participate in the trial. Thus, we expect to recruit 72 participants into the trial, and follow-up 60 participants (30 in each trial arm).

Inviting 570 participants is sufficient to estimate a participation rate (as percentage of subjects invited) of 10 % with a margin of error of +/− 2.46 %, or to estimate a participation rate of 12 % with a margin of error of +/− 2.67 %, or to estimate a participation rate of 15 % with a margin of error of +/− 2.93 %, based on 95 % confidence intervals. Recruiting 72 participants is sufficient to estimate a follow-up rate (as percentage of participants randomised) of 80 % with a margin of error of +/− 9.24 %, or to estimate a follow-up rate of 85 % with a margin of error of +/− 8.25 %, based on 95 % confidence intervals.

In addition, we will calculate the standard deviation of participant outcomes and the correlation between baseline and four month follow-up scores, which can be used to refine future sample size calculations to incorporate the additional precision obtained from adjusting for baseline scores when comparing outcome scores between the trial arms. 30 participants in each group is sufficient to estimate: (i) the standard deviation of continuous outcomes to within 22 % of their true value based on the upper limit of the 95 % confidence interval; (ii) a Pearson’s correlation coefficient between baseline and follow-up scores with a margin of error of +/− 0.1 if the true correlation is 0.8, or with a margin of error of +/− .14 if the true correlation is 0.7, or with a margin of error of +/− 0.17 if the true correlation is 0.6.

30 participants per group is also in line with the general rule of thumb for using pilot studies to reliably estimate variance for participant outcomes [26]. With these factors in mind, we consider 60 participants at follow-up to be both sufficient to provide useful information and reasonable to recruit for within the constraints of our pilot trial and have, therefore, selected 72 as our target sample size, inflating our sample by 20 % to take account of predicted attrition.

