### Criteria for success

The criteria to be met in order to deem a fully-powered RCT feasible as is [20] are:A sufficient number of participants to populate a fully-powered trial are likely to be recruited and retained, i.e. we recruit at the rate anticipated in the pilot trial (12 % of those invited) and experience an attrition rate no higher than 20 % of those randomised, in line with our other National Institute of Health Research (NIHR) mental health trials [21–23]. We will consider whether protocol modification or close monitoring during a fully-powered RCT will address any failure to meet these criteria [20].The levels of engagement with and adherence to Morita Therapy are likely to be on par with our other NIHR mental health trials [23], i.e. at least 65 % of patients allocated to Morita Therapy attend at least 40 % of treatment sessions. Any failure to meet this criterion will be considered in the light of participants’ views on the acceptability of Morita Therapy in order to determine whether protocol modification or close monitoring are sufficient to deem a fully-powered RCT feasible [20].It is likely that a Morita Therapy outpatient protocol can be produced which is acceptable to patients and therapists, and deliverable by therapists, as defined by responses to qualitative interviewing.

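### At the plan's own 12 % rate, 570 invitations give about 68 recruits, not 72; a separate slip in the attrition allowance means 72 recruits give about 58 followed up, not 60

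*Protocol article*

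**What the plan says.** The Sample size section bases the calculation on two feasibility criteria: "recruiting at a rate of 12 % of those invited and experiencing an attrition rate no higher than 20 % of those randomised". It then states the expected flow: "We expect to invite a total of 570 participants to participate in the trial. Thus, we expect to recruit 72 participants into the trial", with 60 of them followed up, 30 per arm.

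The same section gives the precision for a participation rate at 570 invitations, including "or to estimate a participation rate of 12 % with a margin of error of +/− 2.67" points, and the precision for a follow-up rate at 72 recruits. It closes by explaining where 72 came from: the authors "selected 72 as our target sample size, inflating our sample by 20 % to take account of predicted attrition".

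The Criteria for success section uses the same two rates to judge whether a full trial is feasible. Recruitment passes if "we recruit at the rate anticipated in the pilot trial (12 % of those invited"), and retention passes if the investigators "experience an attrition rate no higher than 20 % of those randomised". So 12 % is both the planning rate and the success threshold. Rates of 10 % and 15 % appear only as alternative precision scenarios. Table 1 lists 72 as the target sample size.

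**The concern.** The text presents 72 recruits as following from 570 invitations at 12 %, and 60 followed up as following from 72 recruits with 20 % attrition. Neither step holds at the stated rates. The two numbers of recruits were reached by different routes: 72 by working up from 60, and 68 by working down from 570. The wording joins them as if they were one calculation.

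What is at stake is modest but real. The sample size of this pilot is justified by its recruitment and retention rates, not by power. If recruitment runs exactly as anticipated, the invitation count as written leaves the trial about four people short of its target. If attrition also reaches the 20 % limit, about five fewer than the stated 60 are followed up. A reader who used these figures to plan invitations for the full trial would carry the same shortfall forward.

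**Working it through.** **Inputs** (all from the Sample size section unless noted): 570 invited; 12 % recruited (also in Criteria for success); attrition limit 20 % of those randomised (also in Criteria for success); 72 recruited; 60 followed up; 60 inflated by 20 %.

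**1. Reproduce the plan's own margins.** With 1.96 × √(p(1 − p)/n):
- n = 570: 2.46 points at 10 %, 2.67 at 12 %, 2.93 at 15 %.
- n = 72: 9.24 points at 80 %, 8.25 at 85 %.

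All five agree with the document, so 570, 12 % and 72 are the intended figures and none is a misprint.

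**2. Link from invitations to recruits.**
- Expected recruits: 570 × 0.12 = 68.4, which is 3.6 below 72. Rounding up gives only 69.
- Rate needed: 72/570 = 12.63 %, which rounds to 13 %, not 12 %.
- Invitations needed at 12 %: 72/0.12 = 600.
- The precision scenarios do not supply the missing rate: 10 % gives 57 and 15 % gives 85.5.

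**3. Chance of reaching 72 at a true 12 % rate** (exact binomial).
- 570 invitations: P(X ≥ 72) = 0.34.
- 600 invitations: P(X ≥ 72) = 0.52.

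The second figure is the right yardstick, because a plan set at its expected value falls short about half the time anyway. The slip costs the difference between 0.52 and 0.34.

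**4. Link from recruits to follow-up** (a separate slip).
- The plan's step: 60 × 1.20 = 72.
- Allowance for 20 % loss among those randomised: 60/0.80 = 75.
- Check: 72 × 0.80 = 57.6, not 60. The pair 72 and 60 implies attrition of 1 − 60/72 = 16.7 %.

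**5. Both links together.**
- 570 × 0.12 × 0.80 = 54.7, about 55 in all or 27 per arm.
- Shortfall from 60: 60 − 54.72 = 5.28. Of this, 57.6 − 54.72 = 2.88 comes from the invitation number and 60 − 57.6 = 2.40 from the attrition allowance.
- To follow up 60 at both criteria: 60/0.80 = 75 recruits and 75/0.12 = 625 invitations.

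**6. Effect on precision.**
- Follow-up rate at n = 68: ±9.51 points at 80 % (9.24 at 72) and ±8.49 at 85 % (8.25 at 72).
- Participation rate of 12 % at n = 600: ±2.60 points (2.67 at 570).

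**The case against.** The best defence is that 570 is an expectation and not a cap. The target of 72 does not depend on it, since 72 was set by working up from 60. Recruitment was planned for about ten months, and nothing prevents further invitations. The section on participant identification and recruitment also lists website adverts, waiting-room leaflets and an email to former participants, which could supply four more people. This stands as a reason to regard the consequence as small. It does not rescue the statement, because the document derives 72 from a total of 570 invited and gives the other routes no number.

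A second defence is that 20 % is a ceiling, so 55 followed up is the result at that limit and not a forecast. That is fair as regards the success criterion, although the Sample size section also calls the 20 % allowance predicted attrition. With the 16.7 % implied by 60/72, 68.4 recruits would give 57. The first link fails whatever the attrition.

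Three stronger readings are tempting, and the document does not support them:
- *The stated retention margins are too narrow.* They are given for 72 recruits and are correct for 72.
- *The success criterion and the target contradict each other.* The criterion is a rate. Reaching 72 is not a criterion, so enrolling 68 at 12 % breaks no decision rule.
- *The invitation number explains the whole shortfall of 5.3 at follow-up.* It explains 2.9; the rest is the attrition allowance.

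**Conclusion.** The point holds as two distinct arithmetic slips. At the anticipated 12 %, 570 invitations give about 68 recruits and not 72. At 20 % attrition, 72 recruits give 57.6 followed up and not 60. Combined, the stated rates lead to about 55 followed up. These figures assume that the 570 are the only source of recruits counted, as the text says, and that attrition sits exactly at its limit; the 0.34 and 0.52 also assume independent responses at a true rate of 12 %.

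The size is about four recruits, and 0.27 of a point on the margin for 80 % follow-up. A reader might infer that the pilot's design is undermined. It is not: no hypothesis is tested, the number of invitations can be raised, and no feasibility rule changes. Severity is minor to should-fix.

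**What to change.** Make the chain consistent at both links, in one of two ways.

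- **Keep 570 invitations.** Restate the expectation as about 68 randomised and about 55 followed up at the 20 % attrition limit. Recompute the precision figures at those numbers: ±9.51 and ±8.49 points for follow-up rates of 80 % and 85 %, with the standard-deviation and correlation statements redone for the smaller follow-up number. Say how this expectation relates to the target of 72 in Table 1. The cost is wording only.
- **Keep the target of 72.** State 600 invitations, with a margin of about ±2.60 points at 12 %, and restate expected follow-up as about 58 at 20 % attrition. The cost is 30 more letters, or five for each of the six practices, and enrolment stays at the stated target.

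Moving to 600 invitations alone does not restore 60 followed up. If 60 at both criteria is wanted, the figures are 75 recruits and 625 invitations, which would raise the target itself. In either option, describe the attrition allowance as division by 0.80, or state the 16.7 % that the pair 72 and 60 implies.

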**Methods/Design:**

The Morita Trial is a mixed methods study addressing the uncertainties associated with an evaluation of Morita Therapy compared with treatment as usual for depression and anxiety. We will undertake a pilot randomised controlled trial with embedded qualitative study. Sixty participants with major depressive disorder, with or without anxiety disorders, will be recruited predominantly from General Practice record searches and randomised to receive Morita Therapy plus treatment as usual or treatment as usual alone. Morita Therapy will be delivered by accredited psychological therapists. We will collect quantitative data on depressive symptoms, general anxiety, attitudes and quality of life at baseline and four month follow-up to inform future sample size calculations; and rates of recruitment, retention and treatment adherence to assess feasibility. We will undertake qualitative interviews in parallel with the trial, to explore people’s views of Morita Therapy. We will conduct separate and integrated analyses on the quantitative and qualitative data.

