## Background

Clinical depression and generalised anxiety disorder are the two most common mental health disorders [1], with one in six people in the UK experiencing such a disorder each year [2]. Together, depression and anxiety are estimated to cost the UK economy £17bn in lost output and direct health care costs annually, with a £9bn impact on the Exchequer through benefit payments and lost tax receipts [3].

**Table 1 Tab1:** World Health Organization Trial Registration Data Set

Data category	Information
Primary registry and trial identifying number	Current Controlled Trials database
	ISRCTN17544090
Date of registration in primary registry	23-Jul-15
Secondary identifying numbers	N/A
Source(s) of monetary or material support	University of Exeter Medical School, UK
Primary sponsor	University of Exeter, UK
Secondary sponsor(s)	N/A
Contact for public queries	[name]
	University of Exeter Medical School, UK
	[contact]
Contact for scientific queries	[name]
	University of Exeter Medical School, UK
	[contact]
Public title	The Morita Trial
Scientific title	Morita Therapy for Depression and Anxiety: A Feasibility and Pilot Study
Countries of recruitment	UK
Health condition(s) or problem(s) studied	Depression
Intervention(s)	Morita Therapy
	Treatment as usual
Key inclusion and exclusion criteria	Ages eligible for study: ≥18 years;
	Sexes eligible for study: both;
	Accepts healthy volunteers: no
	Inclusion criteria: adult patient (≥18 years), current DSM Major Depressive Disorder
	Exclusion criteria: cognitive impairment, bipolar disorder or psychosis/psychotic symptoms, substance dependence, acute suicidal risk, current psychological therapy
Study type	Interventional
	Allocation: randomised intervention model
	Primary purpose: treatment
	Phase II
Date of first enrolment	Sep-15
Target sample size	72
Recruitment status	Recruiting
Primary outcome(s)	Depressive symptoms, generalised anxiety symptoms, quality of life, attitudes (at four-month follow-up); qualitative exploration of acceptability.
Key secondary outcomes	N/A

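### The 20 % attrition allowance is added to 60 (giving 72) rather than taken from those randomised, so 72 yields about 58 at 20 % loss, and the abstract gives sixty as the number randomised; the effect is minor

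*Protocol article*

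**What the plan says.** The Sample size section settles on a number needed at follow-up: "we consider 60 participants at follow-up to be both sufficient to provide useful information and reasonable to recruit". It then explains the recruitment target: the authors "have, therefore, selected 72 as our target sample size, inflating our sample by 20 % to take account of predicted attrition".

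Earlier in the section, the attrition criterion is set as "experiencing an attrition rate no higher than 20 % of those randomised", and the expectation is worded as "Thus, we expect to recruit 72 participants into the trial, and follow-up 60 participants (30 in each trial arm". The Criteria for success section repeats the ceiling: "experience an attrition rate no higher than 20 % of those randomised". In both places the denominator is the number randomised.

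The registration data set (Table 1) gives "Target sample size 72". The abstract, under Methods/Design, says: "Sixty participants with major depressive disorder, with or without anxiety disorders, will be recruited predominantly from General Practice record searches and randomised".

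**The concern.** When attrition is a percentage of those randomised, the number needed at follow-up has to be divided by the retention rate. Adding the same percentage to the follow-up number gives a smaller target. The plan took the second route, so its three figures (72 randomised, 20 % attrition, 60 followed up) cannot all hold at once.

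The abstract adds a second, distinct inconsistency about the same quantity. It gives sixty as the number recruited and randomised, where the body of the article and the registration table give 72.

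At stake is whether a reader can tell how many participants are to be randomised and how many completers the plan expects if attrition reaches its own limit.

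**Working it through.** **Inputs**
- Number wanted at follow-up: 60, or 30 per arm (Sample size).
- Attrition: 20 % of those randomised, worded as a ceiling in Criteria for success and early in Sample size. The closing paragraph of Sample size applies an inflation of 20 % for the attrition it predicts.
- Target randomised: 72 (Sample size; Table 1). Abstract: sixty.

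**Reproducing the plan's 72**
- n × (1 + d) = 60 × 1.20 = 72. This matches exactly.

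**The calculation that fits the plan's definition of attrition**
- n / (1 − d) = 60 / 0.80 = 75. Rounding up within arms, 30 / 0.80 = 37.5, so 38 per arm and 76 in all.

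**What 72 delivers**
- At 20 % attrition: 72 × 0.80 = 57.6, about 58, or 29 per arm.
- Attrition implied by 60 of 72: 1 − 60/72 = 16.7 %.
- Exact binomial chance of at least 60 followed up at 80 % true retention: 0.30 with 72 randomised and 0.57 with 75. At 85 % retention, 72 randomised give 0.72.

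**Which number randomised is planned**

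The article states "Recruiting 72 participants is sufficient to estimate a follow-up rate (as percentage of participants randomised) of 80 % with a margin of error of +/− 9.24" percentage points, and 8.25 points for a rate of 85 %. Using 1.96 × √(p(1 − p)/n):

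| n | margin at p = 0.80 | margin at p = 0.85 |
|---|---|---|
| 72 | 9.24 | 8.25 |
| 60 | 10.12 | 9.03 |

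The printed margins reproduce at 72 and not at 60. So 72 is the planned number randomised, and the abstract's sixty equals the follow-up number.

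**Effect on the printed precision**

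The article's SD figure (within 22 %) reproduces with all completers together: upper factor √(df / χ²(0.025, df)) with df = n − 1. The correlation margins agree, to rounding, with Fisher z half-widths, also with all completers together.

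| Quantity | Printed | n = 60 | n = 58 |
|---|---|---|---|
| SD, upper limit | 22 % | 22.0 % | 22.4 % |
| margin at r = 0.8 | 0.1 | 0.095 | 0.097 |
| margin at r = 0.7 | 0.14 | 0.134 | 0.136 |
| margin at r = 0.6 | 0.17 | 0.166 | 0.169 |

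At 58, every value still rounds to the printed figure (0.134 at n = 60 is the only one slightly below it). The participation margins rest on 570 invited and the follow-up margins on 72 randomised, so neither depends on the number of completers.

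**The case against.** The best defence is that 20 % is a ceiling in two of the three places where it appears. Following up 60 of 72 is 16.7 % attrition, which meets that ceiling, and the section quotes precision for follow-up rates of both 80 % and 85 %, which bracket 83.3 %. At 85 %, 72 would yield 61.2. On this reading, expecting 72 recruited and 60 followed up is not in itself contradictory. That stands as far as it goes. It does not rescue the closing paragraph of the section, which ties 72 to a 20 % inflation for predicted attrition, and no lower planning rate is given.

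The second defence is that the shortfall is trivial in a pilot without hypothesis tests. That also stands: none of the criteria for success requires 60 completers, and the 0.30 chance of reaching 60 has to be read beside 0.57 for the target of 75.

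Two stronger readings are tempting and are not supported:
- A reader might infer that the shortfall undermines the SD precision, because at 29 per arm the upper limit is about 35 %. At the full 30 per arm it is already 34.4 %, so attrition adds only 0.8 points. The gap between 22 % and about 34 % comes from pooling both arms against using one arm, which is a separate matter.
- A reader might infer from the abstract that only 48 would be followed up (60 × 0.80). Table 1, the Sample size section and the margins all rest on 72, so the plan contains no such scenario. The abstract's sixty is most plausibly the follow-up number put in the wrong place.

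**Conclusion.** The point holds as a minor arithmetic and consistency error. On the plan's own definition, 72 randomised with 20 % attrition give about 58 followed up, not 60. The stated 60 corresponds to 16.7 % attrition, and 60 at 20 % would need 75 randomised. The abstract's number randomised conflicts with the rest of the article. The size is about two completers, or three more randomised if 60 at 20 % were to be kept. The conclusion rests on the plan's own denominator (those randomised) and on taking 20 % as the planning rate, as the closing paragraph of Sample size does. If true attrition is 16.7 % or less, 72 is enough on expectation. It does not damage the printed precision, the success criteria or any decision the pilot is meant to inform.

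**What to change.** In the Sample size section, replace the statement about inflating by 20 % with one that says what 72 delivers: 60 at follow-up if attrition is 16.7 %, and about 58 (29 per arm) at the 20 % ceiling, with 75 needed for 60 at 20 %. Adjust the sentence on expected recruitment and follow-up to match. In the abstract, give 72 as the number recruited and randomised and 60 as the number expected at follow-up.

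The cost is wording only, and the printed precision figures need no change on this account. Three more participants (four if each arm is rounded up) would be needed only if the sponsor prefers to keep 60 completers at 20 % attrition.

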#### Participant inclusion criteria

Eligible participants will be aged 18 or over with Diagnostic and Statistical Manual of Mental Disorders (DSM) Major Depressive Disorder, with or without accompanying DSM anxiety disorder(s).

